## Discussion

### Limitations and alternative methods considered

The proposed intervention focuses exclusively on cigarette smoking and is not designed to address the use of electronic nicotine delivery systems (ENDS), poly-tobacco use, or the co-use of tobacco with cannabis or other substances. However, we will be able to explore intervention effects on these other forms of substance use in our analyses. It should also be noted that we are not providing cell phones to participants while they participate in this study; rather, individuals must have a working cell phone that can receive text messages in order to participate. We will be monitoring the number of individuals who screen ineligible for this reason, or have a phone that is lost or stops working during the intervention, as indicators of the feasibility of using TMIs with this population.

In terms of the research design, we initially considered a design in which individuals would be randomly assigned to condition within agency. However, we decided against this design given concerns on the part of the research team and drop-in center staff about implementation challenges (e.g., clients perceiving that they were being refused services that other clients were getting) and the strong potential for contamination across conditions. A group-randomized design was a much better option for this evaluation in that it addressed both of these concerns. We will maximize the comparability of the intervention and control groups by: (1) having each drop-in center serve as both intervention and control site on an alternating basis; and (2) using the same procedures at each drop-in center to identify and recruit participants for the study. In addition, once the data are collected we will conduct preliminary analyses to determine whether the intervention and control groups differ on baseline characteristics. This step is necessary despite randomization because the randomization is not occurring at the individual level. If we observe considerable differences in the intervention and control groups, we will control for these with the addition of covariates into the regression models. We may also consider developing analytic weights using propensity score methods to balance the characteristics of the groups. As mentioned earlier, we will also control for any within-site effects by including site as a fixed effect (dummy coded) within the models.

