#### Preliminary analyses

Although participants will be randomly assigned (in groups of about 5–7 individuals) to either the TMI Adjunct or Standard Care Alone conditions, imbalance between the two groups on some of the baseline characteristics may occur. However, since assignment to treatment condition is random, any differences that arise are due to random chance [57, 58]. We will present balance tables of baseline data to confirm the two groups are similar. In all relevant analyses, we will control for variables that are expected to predict the outcome by including them as covariates in the models.

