### Effects of the TMI on smoking behavior

The primary goal of analyses is to assess the promise of the TMI as an adjunct to standard brief cessation counseling and obtain preliminary estimates of intervention effect sizes for a larger trial of the TMI with homeless young people. Given the proposed small sample size, sophisticated modeling that makes adjustments for multiple covariates or potential non-response bias might not be possible; therefore, some analyses will be primarily descriptive.

Biochemically-verified 7-day point prevalence quit rates and self-reported continuous abstinence at 3-months following the baseline visit will be analyzed separately using logistic regression. Logistic regression will also permit modeling the effects of potentially important covariates (e.g., education, age, gender, nicotine dependence, smoking history). We will also compare average number of days smoked by comparing the 30 days immediately prior to the smoking cessation counseling session to the 30 days after the participant’s target quit date. We will fit a regression model to explain the difference in pre and post-intervention outcome by the randomization group indicator (TMI Adjunct vs. Standard Care Alone). We will also estimate a difference in differences (DID) approach for this outcome, including time (a dummy variable indicating pre- versus post-period), the intervention group indicator, and their interaction, and a random subject effect to properly account for the correlation of the repeated measures on each subject and produce efficient estimates of the intervention effect.

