#### Effects of the TMI on other smoking-related outcomes

As a secondary focus, we will examine estimates of the intervention effect on proximal outcomes/mediators (i.e., factors associated with smoking and motivation to quit among young people experiencing homelessness [9] and areas of focus in the TMI) and assess trends. While the planned sample will not be large enough for detecting statistically significant mediation effects, it will allow us to produce estimates of the intervention effect on proximal outcomes/mediators and assess trends. We will adopt a similar modeling approach to the one just described, using a DID approach, since these variables will be measured at both baseline and follow-up.

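### In the difference-in-differences models, site dummies and baseline covariates entered as main effects do not adjust the TMI estimate; they need interactions with time

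*Protocol article*

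**What the plan says.** The section on effects of the TMI on smoking behavior gives the days-smoked outcome two models. The first is a change-score regression: "We will fit a regression model to explain the difference in pre and post-intervention outcome by the randomization group indicator". The second is a DID model, described as "including time (a dummy variable indicating pre- versus post-period), the intervention group indicator, and their interaction, and a random subject effect". The TMI effect in that model is the time-by-group term.

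The section on other smoking-related outcomes carries the approach over to the proximal outcomes, "using a DID approach, since these variables will be measured at both baseline and follow-up". No other model is named for them.

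Two other places promise adjustment. Preliminary analyses states: "In all relevant analyses, we will control for variables that are expected to predict the outcome by including them as covariates in the models". The Discussion, under limitations and alternative methods, says of considerable baseline differences that "we will control for these with the addition of covariates into the regression models". It commits to "including site as a fixed effect (dummy coded) within the models" and mentions propensity-score weights as something that may be considered. Nowhere does the article mention a covariate-by-time or site-by-time term.

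**The concern.** Site and baseline covariates do not change between a person's two measurements. A main effect shifts both measurements by the same amount, so it drops out of the difference on which the DID estimate rests. An analyst who followed the text as it reads would add the covariates, see them in the output, and report an adjusted TMI effect that is numerically the unadjusted one.

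The Discussion itself says that checking for imbalance is needed because individuals are not the unit randomized. With up to 80 people in groups of about 5 to 7, chance imbalance is realistic. The proximal outcomes would have no working covariate adjustment. For days smoked, the adjusted change-score regression and the nominally adjusted DID could differ only because of how the covariates were coded. The section on missing data also names the DID model as one of its analyses valid under missing at random, so the model carries weight beyond a cross-check.

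**Working it through.** **The plan's own figure.** The article gives no number on this point. Its one calculation (Power Considerations) supplies the design effect used in step 5: 1 + 5 × 0.05 = 1.25, and 36 / 1.25 = 28.8 per condition, as printed.

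**1. Main effects only.** For person *i* at time *t* (0 = pre, 1 = post), with group G and baseline variables X (covariates and site dummies):

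Y(i,t) = b0 + b1·t + b2·G + b3·t·G + θ·X + u(i) + e(i,t)

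Subtracting pre from post:

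D(i) = b1 + b3·G + [e(i,1) − e(i,0)]

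Both θ·X and the subject effect u(i) are gone. The person averages say nothing further about b3, because b2 is free. With complete pairs the estimate of b3 is therefore the difference in mean change between arms, whatever X contains. This is algebra and needs no assumed value.

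**2. With time interactions.** Adding φ·t·X gives D(i) = b1 + b3·G + φ·X + error. This is the covariate-adjusted regression of change on group, so X now adjusts b3.

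**3. Numerical check.** Assumed inputs: 80 people, clusters of 6, 3 sites, a covariate that predicts change and is 0.6 SD apart between arms, true effect -3 days, 150 simulated trials per scenario. Mean estimates:

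| Model | Complete pairs | 10% lost, completely at random | 10% lost, at random |
|---|---|---|---|
| DID, no covariates | -1.303 | -1.293 | -1.486 |
| DID + main effects | -1.303 | -1.287 | -1.433 |
| DID + covariate × time, site × time | -3.172 | -3.153 | -3.196 |
| Change score + covariates and site | -3.172 | -3.149 | -3.200 |

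With complete pairs the largest difference between the first two rows in any trial was 0.00000. In a worked dataset the standard error was also identical (1.3017), so there was no gain in precision. With 10% loss, people with a baseline value only bring in some between-person information. Main effects then moved the estimate by 0.15 to 0.16 day on average and by at most 0.58 day in a single trial. The shift produced by real adjustment was 3.172 − 1.303 = 1.869 days.

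**4. When there is nothing to correct.** If the covariates act equally at both times, the plain DID averaged -3.000 with or without main effects.

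**5. How likely and how large.** Take 40 per arm and assume that the design effect of 1.25 also holds for a baseline covariate. The chance difference between arms then has SD √(2 × 1.25 / 40) = 0.25 covariate SDs. A difference beyond 0.3 SD is |z| > 1.2, about 23% per covariate; beyond 0.5 SD is |z| > 2, about 5%. The error left in the estimate is (effect of the covariate on change, per SD) × (imbalance in SD). That is 0.3 to 0.5 day for each day per SD. At an assumed 3 days per SD it is 0.9 to 1.5 days on a linear scale. The article gives no value for the covariate effect.

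**The case against.** The strongest reply is that a condensed article need not give the form in which each covariate enters each model. Nothing in it rules out time interactions, and a fuller analysis plan may contain them. That is fair as far as it goes. However, the article does list the DID terms and does say how adjustment is made, and read together these do not deliver the control promised. The site wording in particular describes a main effect.

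Several further replies stand and limit the point:

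- A reader might infer that no adjustment happens for days smoked. The documents do not support that: the change-score regression comes first, and covariates and site do adjust it.
- A reader might infer that the DID leaves all imbalance uncontrolled. It does not: differencing removes stable, additive differences between arms and sites (step 4).
- Propensity weights could adjust the DID; a propensity-weighted change score averaged -3.147 in the same simulation. They are optional, so they are not a commitment.
- The article warns that multi-covariate adjustment might not be possible at this sample size, and it presents the proximal outcomes as a secondary focus for estimates and trends. Site control, however, is stated without that reservation.
- The bias figures depend on assumed covariate effects and on an imbalance that has occurred. Over repeated randomizations chance imbalance averages to zero.

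**Conclusion.** The point holds within limits. In the DID analyses, meaning the second analysis of days smoked and the only model named for the proximal outcomes, covariates and site entered as main effects leave the TMI estimate exactly unchanged with complete pairs and nearly unchanged with about 10% loss. What stays uncontrolled is imbalance in factors that predict change, and the hoped-for precision is not gained.

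The complete-pairs result is an identity. The simulated figures and the 0.9 to 1.5 days are illustrations under assumed inputs and should not be read as the bias expected in this trial. Nor does the point touch the main abstinence results, as a reader might infer: continuous abstinence and 7-day point prevalence are analyzed by logistic regression, where covariates act in the ordinary way. It is a correction worth making to secondary analyses and to the labeling of adjusted estimates that are meant to inform a larger trial.

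**What to change.** In the two sections on TMI effects and in the Discussion paragraph on covariate control, state that in every DID model site and each adjustment covariate enter together with their interaction with time. Alternatively, name the covariate-adjusted regression of change as the adjusted analysis; with complete pairs it gives the same estimate. Regressing follow-up on group, baseline value, site and covariates serves the same purpose without being numerically identical (-3.171 against -3.172 in the simulation). Where the DID is kept as the likelihood analysis under missing at random, the time-interaction form retains people seen only at baseline. Plain main effects can stay in the logistic and change-score models.

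Keep the covariate list short and fixed in advance, given at most 80 participants. The cost is wording plus about 2 parameters for site and 1 per covariate in each model. The effect on precision can go either way: the SD of the estimate fell from 1.46 to 1.30 in the simulation above, and rose from 1.95 to 2.02 in another with different assumptions.

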## Conclusion

Young people experiencing homelessness have alarmingly high rates of tobacco use, and are disproportionately affected by tobacco use, yet have been virtually ignored in efforts to reduce tobacco use among young people. This study will make a significant contribution to a very limited literature on cigarette smoking, and approaches to smoking cessation, in the highly vulnerable and underserved population of young people experiencing homelessness. It will be both the first to develop a TMI for smoking cessation, and the first to evaluate a smoking cessation program (of any kind), for young smokers experiencing homelessness. Further, although brief standard smoking cessation counseling and nicotine replacement are both well-established treatments, this study significantly extends research in this area by evaluating whether using a TMI for smoking cessation as an adjunct to brief counseling + nicotine replacement increases cessation rates over and above brief counseling + nicotine replacement alone. Finally, this study will provide valuable new information on TMI utilization patterns among homeless young people that will likely be useful to other researchers and clinicians who work with this population and are considering this mode of intervention delivery for health-related programming, as well as pave the way for the larger planned trial to evaluate the proposed cessation intervention.

## Data Availability

Once collected, deidentified data from this study will be available from the corresponding author on reasonable request 1 year after all aims of the project are completed. Requestors of data will be asked to complete a data-sharing agreement that provides for (1) a commitment to using the data only for research purposes and not to identify any individual participant; (2) a commitment to securing the data using appropriate computer technology; and (3) a commitment to destroying or returning the data after analyses are completed.
